#### 2.4.2. Secondary Outcomes

Secondary outcome measures include the Beck depression inventory (BDI) to evaluate the status of depression, 6 min walking test (6MWT) to determine cardiopulmonary endurance, sit-to-stand test (STS-30) to measure lower-limb muscle endurance, and anthropometric measures, such as body mass index (BMI), thigh circumference, and the fat proportion in the body composition as obtained from the bioimpedance analysis (Tanita MC-780).

A 21-item, self-rated BDI with good reported validity and reliability will be applied to measure the depression status of the participants [18,19]. This BDI includes symptoms of depression such as hopelessness and irritability, cognitions such as guilt or feelings of being punished, as well as physical symptoms such as fatigue, weight loss, and lack of interest in sex. Subjects will rate each question on a 4-point scale. The severity of depression is represented by the summed score that ranges from 0 to 63. Scores of 0–13 indicate minimal depression, 14–19 indicate mild depression, 20–28 indicate moderate depression, and 29–63 indicate severe or major depression.

Physical function such as cardiopulmonary endurance will be assessed with 6MWT, and the muscle endurance of lower limbs will be assessed with STS-30. 6MWT is a self-paced test of walking capacity to reflect the functional ability of daily activities [20]. Participants will walk along a walkway (30 m long, 2 m wide) in a quiet corridor of the hospital. Markers will be placed on the walkway at 5 m intervals. Participants will be instructed to walk as far as they can within a period of 6 min, but are allowed to stop and rest if necessary. STS-30 is an indirect measure of lower-limb muscle strength and endurance [21]. Using a chair without arms placed against the wall to maintain stability, the seat height will be adjusted to allow the thigh to be parallel to the ground. The STS-30 test measures the repeated number of times a patient can stand up and sit down from a chair repeatedly during a 30 s period while their arms are crossed in front of their chest.

### 2.5. Statistical Analysis and Power Estimates

Statistical analyses will be performed using SPSS, version 22.0 (SPSS Inc., Chicago, IL, USA). The Shapiro–Wilk test of normality will be used to evaluate the distribution of each outcome variable. If data are normally distributed, paired t*tests and analysis of variance (ANOVA) will be used. If data are not normally distributed, the Wilcoxon signed-rank test and Kruskal–Wallis test will be used. The preintervention outcome measures will be compared using ANOVA or Kruskal–Wallis test. Paired t-tests or Wilcoxon signed-rank test will be applied to compare differences between pre- and post-tests. After the exercise intervention, intergroup comparisons regarding improvements of outcome measures will be determined using ANOVA or Kruskal–Wallis test.

The G*Power (Germany, version 3.1.9) software will be used for sample size estimation [22]. Based on repeated measures ANOVA, a statistical power of 0.8, a significant level of 0.05, the effect size is 0.35, refs. [23,24,25], and a minimum of 84 participants are required for our study. We noted the likelihood of a high drop-out rate for intradialytic exercise [26].

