## Abstract

Background: Exercise training has positive effects on physical functions and could reduce a sedentary lifestyle for hemodialysis (HD) patients. Given that low-level physical activity increases morbidity and mortality, here, we aimed to determine the effects of an intradialytic exercise program delivered at different frequencies on HD patients in Taiwan. Methods: This study is a prospective, randomized control trial. An intradialytic exercise program will be arranged for patients after receiving their informed consent. Patients will be segregated at random into three groups as follows: (a) three times/week of intradialytic exercise training plus standard care maintenance of HD, (b) two times/week of intradialytic exercise training plus standard care maintenance of HD, or (c) standard care maintenance of HD. Subjects will be followed for 24 weeks. At three time points, 0, 12, and 24 weeks, the primary outcome, the Short-Form 36 score, will be measured. Additional secondary outcomes to be measured are the Beck depression inventory, 6 min walking test, sit-to-stand test, and anthropometric measures such as the body mass index, thigh circumference, and the proportion of fat in the body composition. Conclusions: There is emerging evidence in support of intradialytic exercise improving health-related quality of life for patients on HD. However, the difference in the therapeutic effects between three times per week and twice per week has never been determined. With this study, we anticipate to fill the knowledge gap in the exercise prescription among HD patients.

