#### 2.2.2. Randomization

After signing informed consent, participants will be randomly divided into three groups: (i) 3 times/week of intradialytic exercise training plus usual care maintenance of HD, (ii) 2 times/week of intradialytic exercise training plus usual care maintenance of HD, and (iii) usual care maintenance of HD. Randomization of the allocation sequence will be completed using computer-generated random numbers, while taking age, gender, and diabetes status into consideration. A project assistant will examine the outcome measures, and both the participants and the assistant will not be blindly involved in this study.

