#### 2.4.1. Primary Outcomes

Our primary outcome measure of patients is the Short-Form 36 (SF-36) questionnaire, which evaluates the health-related quality of life of the participants. The validity and reliability of the Chinese version of this questionnaire were confirmed in a previous study [17]. Patients who are illiterate or have visual problems will be provided verbal assistance when completing the questionnaire. The SF-36 questionnaire includes 8 subdomains, namely, vitality, physical function, bodily pain, general health perception, physical role functioning, emotional role functioning, social role functioning, and mental health. The lower the score, the lower the self-rated quality of life. These 8 subdomains are integrated into two domains: the physical component scale (PCS) and the mental component scale (MCS).

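### A Shapiro–Wilk test on the collected outcomes chooses between ANOVA and Kruskal–Wallis, so the primary SF-36 test and estimand are not fixed in advance

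*Protocol article*

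**What the plan says.** Section 2.5 of the protocol article sets a two-step rule. A Shapiro–Wilk "test of normality will be used to evaluate the distribution of each outcome variable". Then: "If data are normally distributed, paired t*tests and analysis of variance (ANOVA) will be used". Otherwise: "If data are not normally distributed, the Wilcoxon signed-rank test and Kruskal–Wallis test will be used". The comparison that matters for a randomized trial follows the same switch: "intergroup comparisons regarding improvements of outcome measures will be determined using ANOVA or Kruskal–Wallis test".

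Section 2.4.1 states that "Our primary outcome measure of patients is the Short-Form 36 (SF-36) questionnaire", and nothing exempts it from the rule. The Abstract gives the visits: "At three time points, 0, 12, and 24 weeks, the primary outcome, the Short-Form 36 score, will be measured". Section 2.2.2 gives the three arms: "participants will be randomly divided into three groups".

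Section 2.5 does not say at what level the normality test is judged, whether it is run on raw scores, change scores or residuals, whether arms are pooled, or whether it is run once per outcome or again at each visit. It names no group difference and no confidence interval in either branch.

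**The concern.** ANOVA compares means and Kruskal–Wallis compares ranks, so they answer different questions. Under this rule, the question put to the primary outcome depends on the outcome data. Because the details of the gate are unstated, some discretion also remains after the data are seen.

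The gate also looks in the wrong place. ANOVA relies on approximately normal residuals within arms, not on the distribution of the outcome variable as a whole. With about 84/3 = 28 patients per arm (equal allocation assumed), a comparison of means tolerates mild departures, so the gate gives little protection.

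The Introduction, Discussion and Conclusions ask whether a lower exercise frequency does about as well as a higher one. That calls for the size of the difference between the two exercise arms and its precision, on a scale chosen beforehand. An omnibus test on whichever scale the gate selects does not supply this.

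**Working it through.** **Inputs.** From section 2.5: N = 84, alpha 0.05, power 0.80, effect size 0.35 (read as Cohen's f). From section 2.2.2: three arms. From the Abstract: two post-baseline visits. Assumed: equal allocation, Shapiro–Wilk at 0.05 on values pooled over arms, and the outcome distributions and between-visit correlations given below. The article gives no data on the shape of the SF-36 scores.

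**Step 1, the plan's own figure.** One-way ANOVA, three groups, noncentral F with noncentrality N·f² = 84 × 0.35² = 10.29 on 2 and 81 df: power 0.812. The smallest N is 82, or 84 when balanced. So 84 is reproduced and is used below. (Section 2.5 names repeated measures ANOVA as its basis; that is a separate matter.)

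**Step 2, does the gate distort error rates?** 2,000 simulated trials per scenario, 28 per arm:

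| Quantity | Range over scenarios |
|---|---|
| Two-stage type I error | 0.047 to 0.056 |
| Two-stage power at f = 0.35 | 0.78 to 0.85 |
| ANOVA and Kruskal–Wallis disagree, null | 2% to 3% |
| ANOVA and Kruskal–Wallis disagree, f = 0.35 | 5% to 8% |

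The null scenarios were normal, t with 5 df, two degrees of gamma skew, and a ceiling at +1 SD. The f = 0.35 scenarios were the same without the t. Error rates stay near nominal.

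**Step 3, how often does the gate switch?** This depends on what is tested. Margins were gamma with skewness 0.5 or 0.7, or t with 5 df; between-visit correlation was 0.5 to 0.7; N = 84.

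| Gate applied to | Sent to rank tests | Weeks 12 and 24 get different tests |
|---|---|---|
| Raw scores, all three margins | 34% to 63% | 37% to 49% |
| Change scores, skewed margins | 8% to 13% | 16% to 23% |
| Change scores, t with 5 df | 29% to 32% | 33% to 35% |

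The ends of these ranges are good to about 2 percentage points. Differencing removes most of a shared skew, which explains the gap between rows one and two.

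**Step 4, reading the last column.** If visits were independent and each was sent to ranks with probability p, they would differ with probability 2p(1 − p), which cannot exceed 50%. With p = 0.613, 2 × 0.613 × 0.387 = 0.47. Mild non-normality puts p near the peak. Away from it the figure falls: in independent-visit runs it was 9% for normal data, 15% for stronger skew (gamma shape 4, rejection 91%) and 0.4% with the ceiling (rejection about 100%). In those last two cases both visits mostly go to ranks.

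**Step 5, what each branch reports.** Kruskal–Wallis yields no mean difference. The omnibus ANOVA as written reports none either, and it uses no covariate.

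**The case against.** The best case for leaving the text alone is that the rule does little measurable damage. Type I error and power are near their planned values, and the choice of branch seldom changes significance. That stands, and it limits the point. A reader might infer that choosing a test after looking at the data inflates false positives here; the simulations do not support that.

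Second, section 2.5 compares improvements between groups, so the variable analysed is change, and a gate on change scores fires much less often under skew. This also stands. A reader might infer that about half of all trials would land on ranks, or would use different tests at the two visits. That needs the raw-score reading and distributions near the peak of 2p(1 − p). Per-visit testing is itself an inference: the text is silent, and once per outcome is a possible reading.

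Third, a reader might multiply over the eight SF-36 subdomains and two component scales, 1 − 0.95^10 = 0.40, and conclude that even with normal data some score goes to ranks 40% of the time. That treats the ten scores as independent, yet section 2.4.1 says the subdomains feed the two component scales.

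Fourth, a reader might blame the rank branch alone for the lack of an estimate or of covariates. The stated ANOVA branch has the same gap, and a Kruskal–Wallis p-value does not prevent mean or median differences from being reported alongside it.

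Finally, naming either test in advance would already cure the lack of prespecification. That is true, but it would not give the between-frequency estimate that the trial's question needs. An unseen analysis plan does not answer the point, because the article states a rule rather than leaving one open.

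**Conclusion.** The point holds as a defect of prespecification and should be corrected. By the plain text of section 2.5, the primary SF-36 comparison may be of means or of ranks depending on the collected data, and nothing prevents the answer from differing between weeks 12 and 24. The consequence is an unfixed test and estimand; disagreement on significance is confined to about 2% to 8% of trials.

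The switching rates are illustrations, not predictions. They rest on assumed distributions, equal allocation, a 0.05 gate on pooled values and between-visit correlation of 0.5 to 0.7. The t figures for change scores also depend on how visits are linked. If the visits were jointly multivariate t with 5 df, the change score would itself be t with 5 df, and the gate would fire about as often as on raw values (about 50%).

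**What to change.** In section 2.5, delete the Shapiro–Wilk gate and fix one primary analysis whatever the distribution. Wording along these lines would do:

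*The SF-36 score will be analysed with a linear model containing randomized group and the baseline value of the same score, irrespective of its distribution. The mean difference between the twice-weekly and three-times-weekly groups will be reported with a 95% confidence interval based on HC3 robust standard errors (or the bootstrap). A Kruskal–Wallis test will be reported as a sensitivity analysis only.*

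The cost is a change of wording. Baseline SF-36 is already collected, so no extra data are needed. N = 84 stands for a prespecified ANOVA (power 0.812), whereas prespecifying Kruskal–Wallis instead would need about 84/0.955 = 88 under normality. The downside is slightly less power than ranks if an outcome is very heavy-tailed.

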## 4. Conclusions

In summary, our protocol will evaluate the therapeutic effects of intradialytic exercise programs for HD patients given at different frequencies. With our results, we should be able to determine whether lowering the frequency of intradialytic exercise brings similar therapeutic effects in the Asian population of Taiwan.

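### Within-arm pre-post tests stand beside an omnibus between-arm test, with no statement of which carries the conclusion; read side by side, they would often make equally effective frequencies look different

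*Protocol article*

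**What the plan says.** Section 2.5 (Statistical Analysis and Power Estimates) sets out two kinds of outcome test in consecutive sentences.

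- Within arm: a paired t-test or its signed-rank counterpart "will be applied to compare differences between pre- and post-tests".
- Between arms: "intergroup comparisons regarding improvements of outcome measures will be determined using ANOVA or Kruskal–Wallis test".

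The section does not rank the two, does not limit the paired tests to description, and names no pairwise comparison of arms. It does not say to which arms or which follow-up visits the paired tests apply.

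The purpose of the trial is comparative. The Conclusions state that "our protocol will evaluate the therapeutic effects of intradialytic exercise programs for HD patients given at different frequencies", and that the results should show whether a lower frequency does about as well. Section 2.2.2 randomises participants to three sessions a week, two sessions a week or usual care, and says that "both the participants and the assistant will not be blindly involved in this study". The primary outcome, in section 2.4.1, is the self-rated SF-36.

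**The concern.** A paired test asks whether one arm changed from its own baseline. It makes no use of the randomised usual-care arm, so a time trend, regression to the mean or the expectation of participants who know their allocation counts as change just as an exercise effect would.

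The between-arm test does use the randomisation. As described, however, it is a single test over three groups, and a significant result does not say whether the two exercise arms differ from each other or only from usual care. The paired tests are therefore the only analyses in the text that give a result for each arm. That makes it easy to read a significant change with three sessions and a non-significant change with two as a frequency effect, or to credit exercise with a change that usual care shares. Neither reading is a valid comparison of arms.

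**Working it through.** **The plan's own figure.** Section 2.5 gives "a statistical power of 0.8, a significant level of 0.05, the effect size is 0.35" and concludes that "a minimum of 84 participants are required for our study". A one-way ANOVA with 3 groups, Cohen's f = 0.35, alpha 0.05 and noncentrality λ = f²N needs N = 82 for 80% power (0.801). Rounding up to equal arms gives 84 (power 0.812). So 84 reproduces, if the effect size is read as f. The section says "Based on repeated measures ANOVA", and that method reaches 84 only as the correlation between visits approaches 1. This mismatch is a separate matter. All that is used here is 84 / 3 = 28 per arm.

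**Inputs**
- 28 per arm: from 84, assuming equal allocation and no dropout. The article states neither a ratio nor a dropout rate.
- Two-sided 5% level: 0.05 is stated; two-sidedness is assumed.
- Within-arm change in SD of the change score (dz): not in the article, so assumed over 0.2 to 0.8.

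**Formulas**
- Power of one paired t-test: p = P(|T| > t₀.₉₇₅,ₙ₋₁), where T is noncentral t with n − 1 degrees of freedom and noncentrality dz√n.
- Two exercise arms with the same true change, exactly one significant: 2p(1 − p).
- All three arms with the same true change (no exercise effect), at least one exercise arm significant and usual care not: with q = 1 − p, this is q(1 − q²).

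**Results, 28 per arm**

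| dz | p | 2p(1 − p) | q(1 − q²) |
|---|---|---|---|
| 0.2 | 0.175 | 29% | 26% |
| 0.3 | 0.334 | 45% | 37% |
| 0.4 | 0.532 | 50% | 37% |
| 0.5 | 0.723 | 40% | 26% |
| 0.6 | 0.864 | 23% | 13% |
| 0.7 | 0.946 | 10% | 5% |
| 0.8 | 0.983 | 3% | 2% |

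Worked row for dz = 0.3: 2 × 0.334 × 0.666 = 0.445; 0.666 × (1 − 0.666²) = 0.666 × 0.556 = 0.371.

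The first probability peaks at 50% near dz = 0.38. The second peaks at 38.5% near dz = 0.35.

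**Dropout.** Section 2.5 expects dropout to be high without giving a rate. With 22 per arm (assumed, about 20% lost), 2p(1 − p) is 25% at dz 0.2, 36% at 0.6 and 21% at 0.7. With 20 per arm (assumed, about 29% lost), it is 24%, 40% and 26%. Smaller arms move the problem towards larger changes.

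**Benchmark.** In 40,000 simulated trials with equal true change, a two-sample t-test of change between the exercise arms was significant in 4.9% to 5.1%, and the three-arm ANOVA in 4.8% to 5.1%.

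**Multiplicity of the alternative.** Three unadjusted pairwise 5% tests among three equal arms of 28 (pooled variance, 81 degrees of freedom) give at least one false positive in about 12% of trials, from the studentised range: P(range > √2 × t₀.₉₇₅,₈₁) = 0.121. Pairwise differences therefore need a stated rule.

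**The case against.** The strongest reply is that the plan already contains a valid between-arm test of improvements, usual care included, and nowhere gives the paired tests a confirmatory role. A reader might infer that the paired tests are intended as the evidence of benefit, or that the plan discards the randomised comparison. The text supports neither reading. The percentages above describe what happens if the paired results are read side by side, which the article does not say it will do.

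It is also fair to say that the size of the problem depends on the assumed change. Between 0.2 and 0.4 SD the assumption brackets the peak, and by 0.8 SD the problem is almost gone. A reader might also count every disagreement among three equal arms, which gives 1 − p³ − q³, or 43% to 75% at 0.2 to 0.4 SD. That includes patterns such as usual care alone being significant, so it overstates the risk that matters here.

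Finally, lack of blinding can bias between-arm differences in a self-rated outcome as well, and removing the paired tests does not cure that.

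These points stand and limit the claim. They do not remove it. The paired tests are a stated analysis, so their presence cannot be put down to detail left to an unseen plan. The only between-arm test described cannot by itself answer the question of three sessions against two.

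**Conclusion.** The point holds in a limited form. Section 2.5 lists within-arm tests and an omnibus between-arm test without saying which one supports conclusions on benefit and frequency, and only the within-arm tests give a result for each arm.

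Read side by side, they would give two equally effective frequencies different verdicts in about 23% to 50% of trials for changes of 0.2 to 0.6 SD. With an equal change in all three arms, they would favour at least one exercise arm over usual care in 26% of trials at 0.2 SD and 37% at 0.3 and 0.4 SD. A between-arm test errs in 5%.

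These figures rest on assumed standardised changes, equal allocation, no dropout and independent arms. The trial is not invalidated, because a valid overall test is planned. What is exposed is the conclusion on frequency.

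**What to change.** State in the analysis section that within-arm changes are descriptive, and show them as mean change with 95% CI by arm without p-values. Base every statement on benefit or frequency on the randomised comparison: the overall three-arm test first, then baseline-adjusted differences for three sessions minus usual care, two sessions minus usual care, and three minus two sessions, each with a CI.

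State the multiplicity rule. One option is to test pairs only after a significant overall test, which with exactly three arms holds the familywise error of the tests at about 5%. If the intervals are to have joint coverage, adjust them as well.

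The cost is a few sentences, slightly more analysis and wider adjusted intervals. No new data or participants are needed for this change. It does not deal with bias from open-label, self-rated assessment, which should be acknowledged as a limitation.

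### The between-arm test is a valid but inefficient unadjusted comparison of improvements; adjusting for the baseline score and the randomisation factors would recover power at almost no cost.

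*Protocol article*

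**What the plan says.** Section 2.5 of the protocol article fixes the between-arm method: "After the exercise intervention, intergroup comparisons regarding improvements of outcome measures will be determined using ANOVA", or Kruskal–Wallis where the data are not normal. The choice between the two tests follows a Shapiro–Wilk test. Baseline values get a separate comparison: "The preintervention outcome measures will be compared using ANOVA or Kruskal–Wallis test". Within-arm change is examined by paired tests. No covariate is named in any of these analyses. Repeated measures ANOVA appears only in the sample-size paragraph, also without covariates.

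Section 2.2.2 says that allocation uses "computer-generated random numbers, while taking age, gender, and diabetes status into consideration". These three factors are not mentioned again in Section 2.5. The Abstract confirms that a baseline value of the primary outcome will exist: "At three time points, 0, 12, and 24 weeks, the primary outcome, the Short-Form 36 score, will be measured".

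**The concern.** Baseline has two roles in the plan. It is subtracted to form the improvement, and it is tested between arms. Neither is the efficient use. Subtraction imposes a slope of 1 on the baseline score, whereas the best-fitting slope is normally below 1. The excess appears as extra residual variance and as sensitivity to chance baseline differences, which are not negligible at about 28 patients per arm (84/3, if allocation is equal).

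Testing baseline values between randomised arms addresses a null hypothesis that is true by design. The result cannot correct an imbalance, and the plan does not say what would follow from a significant one.

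Three things raise the stakes here. The planned power is only just above 0.8. Section 2.5 expects high drop-out but states no inflation for it. And the question of interest, two versus three sessions a week (Discussion and Conclusions), needs a precise estimate: a non-significant difference with a wide interval would not show that the two frequencies have similar effects.

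**Working it through.** **Inputs from Section 2.5:** effect size 0.35 (read here as Cohen's f, which the text does not say), significance level 0.05, power 0.8, total N 84. There are three arms (Section 2.2.2).

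**Assumptions, not in the documents:** equal allocation; equal variance σ² at baseline and follow-up; the correlation ρ; and, for one illustration, 20% drop-out.

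**1. The plan's own figure.** For a one-way ANOVA with three arms, the noncentrality is λ = f²N with (2, N−3) degrees of freedom.
- N = 81: power 0.796.
- N = 84: λ = 0.35² × 84 = 10.29, power 0.812.

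So 84 is the smallest balanced N for an unadjusted one-way ANOVA. That gives a fair reference point for the unadjusted test on improvements.

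**2. Residual variance of the two analyses.**
- Change score: 2σ²(1−ρ).
- ANCOVA on baseline: σ²(1−ρ²).
- Ratio: (1−ρ²) / [2(1−ρ)] = (1+ρ)/2, which is below 1 for every ρ below 1.

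**3. Power with f = 0.35 on change.** Under ANCOVA, f becomes 0.35/√[(1+ρ)/2]. Four covariate degrees of freedom are spent (baseline, age, gender, diabetes), and no credit is taken for any prognostic value of the last three. The 67 completers are 84 × 0.8.

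| ρ (assumed) | Variance ratio | f under ANCOVA | Power, N = 84 | Power, 67 completers |
|---|---|---|---|---|
| change score | 1 | 0.350 | 0.81 | 0.71 |
| 0.3 | 0.65 | 0.434 | 0.95 | 0.88 |
| 0.5 | 0.75 | 0.404 | 0.91 | 0.83 |
| 0.6 | 0.80 | 0.391 | 0.89 | 0.81 |
| 0.7 | 0.85 | 0.380 | 0.87 | 0.78 |
| 0.8 | 0.90 | 0.369 | 0.85 | 0.75 |
| 0.9 | 0.95 | 0.359 | 0.83 | 0.73 |

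At N = 84, spending four covariate degrees of freedom instead of one lowers power by about 0.001 at most. For pairwise differences, interval width shrinks by about √[(1+ρ)/2], which is 0.87, 0.89 and 0.92 at ρ of 0.5, 0.6 and 0.7.

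**4. If f = 0.35 refers to the follow-up score instead.** Power at N = 84 for change versus ANCOVA is then 0.66 versus 0.85 at ρ = 0.3, 0.81 versus 0.91 at 0.5, and 0.96 versus 0.98 at 0.7.

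**5. The randomisation factors.** Leaving out a factor on which allocation was balanced makes a test conservative only to the extent that the factor explains variance in the variable tested, which here is change. In a simulation with 28 per arm, ρ = 0.6 and one perfectly balanced factor explaining 10% of outcome variance at both times, the unadjusted test on change rejected a true null about 5% of the time, which is its nominal level. A factor that shifts baseline and follow-up equally cancels out of the difference.

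**The case against.** The strongest reply is that nothing here is invalid. ANOVA on change in a randomised trial gives an unbiased comparison, a change score does use baseline, and covariates are often left to a fuller analysis plan. The first two points stand: the issue is efficiency, and it would be wrong to say that the plan ignores baseline. The third carries less weight, because the article does not stay silent on the method. It names the between-arm test, and neither ANOVA nor Kruskal–Wallis on improvements adjusts for anything.

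A second reply is that the gain depends on an unstated ρ and on how f is read. This also stands as a limit on size. At ρ = 0.9, power moves only from 0.81 to 0.83, and if f refers to the follow-up score the gain at ρ = 0.7 is small. The direction does not depend on these assumptions.

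A reader might go further and infer that omitting age, gender and diabetes makes the standard errors too large and the 5% test conservative. The documents do not support that. It would require allocation to have been restricted on these factors and the factors to predict change. Section 2.2.2 says only that randomisation proceeds "while taking age, gender, and diabetes status into consideration", without naming stratification or minimisation, and nothing is said about whether they predict change. Likewise, the plan states no data-driven response to a baseline imbalance. The baseline tests are uninformative, but it cannot be said that they will lead to ad hoc adjustment.

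**Conclusion.** The point holds as a recoverable loss of efficiency, not as bias or an error in the level of the test. ANCOVA on baseline has (1+ρ)/2 of the residual variance of the planned change-score comparison, a reduction of 15% to 25% at ρ from 0.7 down to 0.5. The resulting gain at N = 84 is about 6 to 10 percentage points of power over that range, and about 2 to 14 points over ρ from 0.3 to 0.9, if f = 0.35 applies to change. With an assumed 20% drop-out, the unadjusted test falls to 0.71, and adjustment restores it to between 0.78 and 0.83 at ρ from 0.7 to 0.5.

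The case for including age, gender and diabetes is weaker but sufficient: it follows the stated randomisation and costs almost nothing. Any further gain depends on their prognostic strength, which is not given. This should be changed, but the trial would not be invalid without it.

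**What to change.** - Make the primary between-arm analysis a linear model for the SF-36 score with arm, the baseline value of that score, age, gender and diabetes. Use either ANCOVA or a mixed model over weeks 12 and 24. Report adjusted pairwise differences with 95% confidence intervals.
- Use the same model for the BDI, 6MWT, STS-30 and anthropometric outcomes, each with its own baseline value.
- Keep this model as primary whatever the Shapiro–Wilk result. Replace the Kruskal–Wallis branch with a rank-based or robust version as a sensitivity analysis.
- Remove the significance tests of baseline values and present them descriptively by arm.
- Set this down before outcome data are compared by arm.

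The cost is a change of wording and four covariate degrees of freedom. Baseline outcomes are already measured, the three factors are needed for allocation, and SPSS fits the model. The one new decision is how age enters, which should be fixed in advance.
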